## Abstract

**Background:**

The prevalence of smoking is higher among Pakistani and Bangladeshi males than among the general population. Smokers who receive behavioural support and medication quadruple their chances of stopping smoking, but evidence suggests that these populations do not use National Health Service run stop smoking clinics as frequently as would be expected given their high prevalence of smoking. This study aims to tackle some of the main barriers to use of stop smoking services and adherence to treatment programmes by redesigning service delivery to be more acceptable to these adult male populations. The study compares the effectiveness of trained Pakistani and Bangladeshi smoking cessation workers operating in an outreach capacity ('clinic + outreach') with standard care ('clinic only') to improve access to and success of National Health Service smoking cessation services.

**Methods/design:**

This is a pilot cluster randomised controlled trial based in Birmingham, UK. Super output areas of Birmingham will be identified in which more than 10% of the population are of Pakistani and/or Bangladeshi origin. From these areas, 'natural geographical communities' will be identified. Sixteen aggregated agglomerations of super output areas will be identified, separating areas from each other using buffer regions in order to reduce potential contamination. These natural communities will be randomised to 'clinic + outreach' (intervention) or 'clinic only' (control) arms. The use of stop smoking services and the numbers of people quitting smoking (defined as prolonged self-reported abstinence at four weeks, three months and six months) will be assessed in each area. In addition, we will assess the impact of the intervention on adherence to smoking cessation treatments and patient satisfaction.

**Trial registration:**

Current Controlled Trials ISRCTN 82127540.

## Background

### The problem being addressed

The UK has a national network of National Health Service (NHS) smoking cessation services offering a range of interventions proven to be effective in facilitating smoking cessation. Those using these cessation services are four times more likely to succeed in quitting than those who attempt to stop smoking on their own[1]. Bangladeshi and Pakistani males, who have a high prevalence of smoking[2] are however half as likely as the White population to use these services[3,4]. This may be because Bangladeshi and Pakistani smokers are poorly served by current smoking cessation services. One possibility is that existing service formulations need to be adapted to better meet the needs of these minority populations.

This study aims to provide key components of the evidence base for promoting effective smoking cessation in these two large minority ethnic communities comprising over one million UK citizens (1.8% of the UK population)[5]. Bangladeshis and Pakistanis are two of the most socio-economically deprived and marginalised communities in the UK with persistent poor health outcomes for a range of long-term disorders. Stopping smoking is especially important in these populations as Pakistani and Bangladeshi groups are at significantly increased risk of heart disease, stroke and type 2 diabetes when compared to the White population[6,7]; stopping smoking would reduce the risk of these conditions by at least one-third[8,9].

We have been pursuing a phased programme of work[3,10,11], in line with the Medical Research Council's (MRC) complex intervention framework, studying smoking behaviour in these communities which we seek to advance to a definitive (Phase III) trial stage [12-14]. The work reported here seeks to refine and pilot a theoretically informed, culturally acceptable, trained community smoking cessation worker model of care suitable for subsequent formal evaluation in a multi-centre cluster randomised controlled trial[12].

We are focusing on these two ethnic groups because of the high prevalence of smoking, the shared religious tradition[15], the high disease burden from cardiovascular, cerebrovascular and respiratory disorders[16], and our collective expertise in researching these communities. It is anticipated that the insights gleaned from in-depth work with these populations will provide important transferable lessons for future smoking cessation work in other minority ethnic groups.

### Smoking prevalence in ethnic minority communities

Data from the 2004 Health Survey for England revealed marked ethnic and gender variations in smoking patterns, with cigarette smoking prevalence being particularly high amongst Bangladeshi men (40%, compared with the national average of 24%)[2]. Smoking prevalence in Pakistani males (29%) was somewhat higher than the national average. This was in stark contrast to smoking figures in Pakistani (5%) and Bangladeshi (2%) women, which were significantly lower than the national average for women (23%). Similarly, smoking prevalence in males was particularly high in Bangladesh and Pakistan[17].

The English national smoking cessation services collect data quarterly on ethnicity using very broad ethnic groupings. Although 2.3% of English smokers are 'Asian'[4], only 1% of clinic users were classified as being 'Asian'[18], raising uncertainty over whether the national network of services is able to attract and meet the needs of these populations. Parts of Birmingham (and some other cities in the UK) have begun to develop models of care similar to those that are proposed in this study; these are however being implemented on a somewhat ad hoc basis, without clear evidence of effectiveness, and without rigorous evaluation.

Systematic reviews and meta-analyses have found that behavioural (counselling)[19] and some pharmacological interventions [20-22] increase the likelihood of successful smoking cessation and these findings have been incorporated into evidence-based guidelines for smoking cessation [23-25].

Although increasing smoking cessation remains a national priority[26], these effective interventions are underused within ethnic minority communities[3]. There is thus at present little evidence on how effectively to facilitate smoking cessation in Bangladeshi and Pakistani communities. There has, perhaps as a consequence, been few attempts to specifically target or tailor smoking cessation services to meet the needs of these communities[27,28]. This is of concern as qualitative work (using in-depth interviews and focus groups), has shown that culture and religion are strong influences on smoking attitudes and behaviours[3]. There was found to be widespread awareness of the dangers of smoking and a high degree of motivation to quit, with many quit attempts; these however tended to rely on "willpower" alone and were (unsurprisingly) typically unsuccessful. Knowledge of, beliefs about and limited access to known effective smoking cessation interventions were shown to be important cultural and structural barriers to improving quit rates. The authors proposed that services should be flexible, multi-lingual, supportive and involve local people in their delivery.

Although many smokers also emphasised the importance of religious centre based services, a telephone survey of a random sample of 50 British mosques found that whilst most would like to support smokers to quit, few Imams (religious leaders) believe that their centres currently have the capacity to support this work making a mosque-based intervention unfeasible at present. Similarly, our enquiries have found that the prospects of a Fatwa (religious edict) – something which qualitative work also suggested might be useful to help smokers quit – is also very unlikely in the near future in Britain ([name], Chair of Mosque and Community Affairs Committee, Muslim Council of Britain, personal communication, 2005) and even in countries where such Fatwas have been issued the impact of these has, at best, been extremely limited[29].

### Rationale for this trial

Our enquiries, the qualitative work already undertaken, and the experiences of services that have begun to develop new styles of smoking cessation service delivery suggest that "grass-roots" trained community smoking cessation worker delivered interventions are likely to prove feasible, accessible and effective.

This study seeks to build on these insights and develop and then pilot a model of community stop smoking services that will be "owned by" and prove acceptable to Bangladeshi and Pakistani male smokers, and their wider communities. Our enquiries indicate that there are several models of care centred on bi- or multi-lingual trained community smoking cessation workers currently in existence. These range, for example, from facilitators focusing on improving access to existing mainstream smoking cessation services to developing home-based specialist parallel services. It is, however, important to prioritise the evaluation of interventions that are potentially generalisable across the NHS hence the focus here is on interventions that have the potential to integrate with existing smoking cessation services.

### Aims and study questions

#### Aim

To develop and investigate the potential of a culturally appropriate community smoking cessation service in improving access to and the effectiveness of smoking cessation services for male adult Pakistani and Bangladeshi smokers.

#### Study questions

Primary study questions:

1. What are the rates at which the population of Pakistani and Bangladeshi male smokers will set a quit date with the stop smoking services in the intervention and control areas?

2. What proportions of those setting a quit date in the intervention and control areas achieve biochemically verified prolonged abstinence from smoking at a) 4 weeks, b) 3 months and c) 6 months after the agreed quit date?

3. What is the likely degree of contamination of the intervention and control areas and the design effects that need to be taken into consideration when conducting sample size calculations for a definitive cluster randomised controlled trial?

4. What are the key components of the intervention as it develops and how do these components relate to the outcome measured by the rates of setting quit dates and abstinence among those setting quit dates?

Secondary study questions:

5. What proportion of Pakistani and Bangladeshi male smokers that book an appointment with the stop smoking service attend the initial appointment and set a quit date in the intervention and control areas?

6. What smoking cessation treatments do Pakistani and Bangladeshi men use in the intervention areas, facilitated by outreach workers, and in the control areas, without such workers?

7. What are the experiences of the services of the relevant groups in each of the trial arms and how satisfied are they?

8. What proportions of those enrolled adhere to the interventions chosen?

9. What impact, if any, are these interventions likely to have on smokeless (oral) tobacco use in these smokers?

10. What are the costs, from a health service perspective, of delivering these interventions?

## Methods

### Study/design

This is a pilot cluster randomised controlled trial being undertaken in Birmingham East and North Primary Care Trust (BEN PCT) and the Heart of Birmingham Teaching Primary Care Trust (HoB tPCT). The trial compares the change in the key outcome variables between intervention and control areas. The change is the difference between the intervention period rates of activity in the intervention area and the same period one year prior to the intervention. An analogous figure is calculated for the control areas and the difference in these changes are then compared.

### Interventions

The interventions being tested in this two arm pilot trial are: (i) standard stop smoking advisor based in smoking cessation clinic ('clinic only' control) *vs*. (ii) community based stop smoking advisor working in an outreach capacity, to support existing clinics enhance the tailoring of smoking cessation treatments to the specific needs of Pakistani and Bangladeshi male smokers and/or to provide smoking cessation treatment themselves in a location of their choosing ('clinic + outreach').

The aim of both models of care is to attract clients, to convince them of the value of behavioural support and pharmacotherapy, to provide these interventions themselves or point people towards clinics providing such treatment, and to persuade clients to persist with treatment until the risk of relapse is substantially decreased.

#### 'Clinic only' (control)

In the areas allocated to the 'clinic only' arm, the NHS stop smoking services will attract clients in the normal way. The model is well developed in BEN PCT and HoB tPCT. The model consists of health care service providers, including general practitioners (GPs), nurses, pharmacists and stop smoking advisors (SSAs) who are trained in smoking cessation, and work to standards set and monitored by the local stop smoking services.

#### 'Clinic + outreach' (intervention)

In areas allocated to the 'clinic + outreach' arm, the NHS stop smoking services will attract clients with additional support from four community based stop smoking advisors, also known as 'outreach workers'. These outreach workers come from the ethnic groups of interest (i.e. two of Bangladeshi origin and two of Pakistani origin) and live in the communities that they serve. Between them, they speak several relevant languages (i.e. Sylheti, Bengali, Punjabi, Mirpuri, Urdu and English).

A specialised training programme for the outreach workers will be organised prior to the start of the intervention, to combine training in smoking cessation with a special understanding of the norms and beliefs about tobacco in the Pakistani and Bangladeshi communities. This will consist of:

◦ Standard two-day SSA training delivered by HoB tPCT

◦ Three-day health promotion training course delivered by HoB tPCT on exploring ways to promote well-being and health, and techniques involved in the planning, preparation and delivery of approaches.

◦ Sessions given by primary care staff at the University of Birmingham on research skills, communication skills, the function of the NHS, the cultural context of the work, and discussion of the outreach role.

We envisage that the outreach workers will take the following approaches to improve the reach of and access to the smoking cessation services:

◦ Undertake community engagement work to help increase awareness of smoking cessation services

◦ Assist existing service providers with the delivery of stop smoking support and promotions

◦ Provide stop smoking support and medication for people in non-clinic venues, e.g. workplaces, public buildings.

Additionally, we envisage that the outreach workers will draw on their in-depth understanding of beliefs about and attitudes towards smoking, in order to:

◦ Raise awareness of the dangers associated with smoking and counsel smokers wishing to quit

◦ Identify suitable quit dates (which may be based on key religious events such as a Friday congregational prayer, journey on Umrah or Hajj (pilgrimage to Mecca), or to coincide with the month of Ramadan, for example)

◦ Highlight religious objections to smoking, where appropriate

◦ Make available existing and custom-made literature, telephone (Asian QuitLine) and other support materials.

We hypothesise that the 'clinic + outreach' model will attract more patients to the service because it is seen as more culturally appropriate. In addition, the service should influence the proportion of people successfully attempting to stop smoking by encouraging patients to persist with treatment.

### Randomisation

We will use census super output areas (SOAs) as the unit of allocation[30]. In order to define these communities, initially all those SOAs within the study area with a combined Bangladeshi and Pakistani population of more than 10% will be identified and then mapped at ward level, enabling the street boundaries of each SOA to be seen. Contiguous SOAs will then be aggregated into natural communities (i.e. areas where people live, work, shop etc) using the local knowledge of the LSSS managers and advisors. SOAs in which more than 30% of the population are Pakistani and Bangladeshi will be considered to be high-density areas, while SOAs with 10–29% of the population being from these groups will be defined as low-density areas.

A total of 16 aggregated areas, sufficiently geographically dispersed, will be created to be randomised; there will thus be eight SOAs in each arm. For the randomisation, we will stratify, firstly by the proportion of Pakistani and Bangladeshi residents and secondly by absolute population size, to create eight areas that include high target population density and eight that are low-density areas. The high density areas will be further subdivided into those areas with target populations of Bangladeshi and Pakistani men above and below 10,000. The low density areas will be further subdivided into those areas with target populations above and below 300. Table 1 shows how the areas will be allocated. Randomisation will be undertaken by the study statistician who has no knowledge of the geographical areas using permuted blocks. Within each of the four strata, two areas will be randomly allocated to 'control' and two to 'intervention' arms. Maps of the final areas and their allocation to the two study arms are shown in Figures 1 and 2.

**Figure 1 F1:**
[figure not shown]
**Map of randomisation areas in HoB tPCT**.

**Figure 2 F2:**
[figure not shown]
**Map of randomisation areas in BEN PCT**.

**Table 1 T1:** Randomisation allocation

Number of areas	Bangladeshi and Pakistani population density	Bangladeshi and Pakistani population size	Study arm
2	High*	<10,000	Clinic only

2	High	<10,000	Clinic + outreach

2	High	>10,000	Clinic only

2	High	>10,000	Clinic + outreach

2	Low**	<300	Clinic only

2	Low	<300	Clinic + outreach

2	Low	>300	Clinic only

2	Low	>300	Clinic + outreach

*Pakistani and Bangladeshi populations = >30%

** Pakistani and Bangladeshi populations = 10–29%

In studies in which the number of units randomised is relatively small, stratified randomisation of communities should ensure equal distribution of key potential confounders. However, potential confounders are also important contextual factors affecting the success or otherwise of the interventions and thus possible effect-modifiers. We will therefore gather data on relevant aspects of the communities (in particular socio-economic position, since this is a strong predictor of smoking status) participating in the trial. Such data will be critical in enabling generalisation of the lessons learnt from this pilot trial.

### Protecting against sources of bias and reducing contamination

The main source of bias in this trial is likely to arise from contamination (i.e. people helped to stop smoking with the aid of the LSSS who live in 'clinic only' areas). The potential for contamination will be reduced by careful planning. First, natural communities will be chosen – places where local intelligence tells us people tend to live *and *work. Second, buffer zones will be created around the trial areas that are neither 'clinic only' or 'clinic + outreach' in order to reduce the possibility of people living in control areas crossing into intervention areas and coming across intervention workers (see Figures 1 and 2). This will mean excluding large areas that have both high and low densities of Pakistani and Bangladeshis living in them that would otherwise have participated in the trial. We will be able to gauge the degree of contamination by using a before-after design. Working with anonymised versions of the LSSS databases, we will analyse data on the use of services by Pakistani and Bangladeshi residents of intervention and control areas and other areas of Birmingham mostly distant from our intervention and control areas. We will thus be able to contrast the change in service use, not simply differences in service use. Contamination would be marked by increases in service use in areas assigned to either the control or special intervention that would not be seen in outside areas that served as the external control. Informal conversations with patients, service providers, and outreach workers will also be carried out to provide additional insight into the extent of any contamination.

The two quantitative primary outcomes are uptake and abstinence rates. Nearly all people contributing data to these rates will be unaware of the trial. Thus the potential for information bias is minimal.

The first three primary study questions will be answered using LSSS data, most of which are collected routinely (LSSS Dataset). The fourth primary question will be answered by a qualitative study, consisting of longitudinal focus group discussions with the outreach workers, observation of their management meetings, analysis of their diaries, and some shadowing of their activities.

The secondary questions will be addressed either through LSSS data on treatments used, or through an Extended Dataset collected from a self-selected sub-sample of participants in the trial (Extended Dataset). Data sources and outcome measures for each of these research questions are summarised in Table 2. The flow of participants through the trial is shown in Figure 3.

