**LSSS Dataset**		

1. What is the rate at which the population of Pakistani and Bangladeshi male smokers will set a quit day with the stop smoking services in the intervention and control areas.	Recruitment rate is defined as the number of relevant population setting a quit day with the services as a fraction of all those estimated to have attempted to stop.	LSSS routine database

2. What proportions of those setting a quit day in the intervention and control areas achieve prolonged abstinence from smoking at a) 4 weeks, b) 3 months and c) 6 months after the agreed quit day?	a) Number of quits (measured by self assessment questionnaire & CO monitoring) Total number of smokers* accessing LSSS b) & c) number of quits (measured by self assessment questionnaire & CO monitoring)	a) LSSS routine database b) & c) LSSS data collected specifically for the trial

3. What is the likely degree of contamination of the intervention and control areas and the design effect that need to be considered when conducting sample size calculations for a definitive cluster randomised controlled trial?	The design effect from cluster randomisation will be calculated from the multilevel analysis. Contamination cannot be easily measured; however, we have external controls which will help indicate whether it is occurring.	

4. What are the key components of the intervention as it develops and how do these components relate to the outcome measured by the rates of setting quit dates and abstinence among those setting quit dates?	Qualitative data	Focus groups with outreach workers Observation of management meetings Shadowing Analysis of outreach worker diaries End of project interviews with outreach workers

5. What proportion of Pakistani and Bangladeshi male smokers that book an appointment with the stop smoking service attend the initial appointment and set a quit day in the intervention and control areas?	To be estimated from a sample of service providers records	SSA records LSSS Routine database

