Area number	Number of Pharmacies	Numbers using any LSSS service 06/07	Number of smokers using LSSS within area they live	Number of smokers using LSSS in other areas of randomisation	Number of smokers* using LSSS users out of study zone	Number of smokers using unidentified LSSS
1	0	7	0	0	7	0

2	1	10	1	0	9	0

3	0	29	0	8	20	1

4	3	79	41	4	32	2

5	5	155	57	2	77	19

6	4	136	43	5	84	4

7	6	98	55	0	42	1

8	2	6	0	1	5	0

9	1	2	0	0	2	0

10	0	4	0	0	3	1

11	0	8	0	5	3	0

12	0	3	0	0	3	0

13	0	11	0	8	2	1

14	1	8	0	3	5	0

15	0	2	0	0	2	0

16	0	5	0	0	5	0

*Bangladeshi or Pakistani Males aged 18 years or over

Although we will estimate the proportion of people setting a quit date, we cannot truly know the denominator, as in many cases people set multiple quit dates, hence we will consider this a rate and the 'denominator' an offset in the analysis.

Quantitative analysis will use a multilevel approach. In this model the outcome variable will be the number of individuals setting a quit date in each of the 16 randomised areas. The quasi-denominator is the estimated number wishing to quit in each area, and the log of this number will be used as an offset in a Poisson regression model. Independent variables in the model will be the group (control or intervention) and the log of the numbers setting a quit date in the previous 12 months before the trial. The randomised areas will be included in the model as a random effect, thereby allowing for the clustering inherent in the design[35]. This will be used in estimating the intra-class correlation coefficient, which in turn will determine the design effect. This is the multiplier which has to be applied to standard sample size formulae to allow for the effect of randomising at the cluster level instead of the individual level[36]. The stratification used in producing the randomisation will not be utilised in the analysis.

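### The contamination rule counts a rise in service use in the intervention areas, which is the hypothesised effect, as contamination, so the contamination half of primary question 3 is answered ambiguously

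*Protocol article*

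**What the plan says.** Primary question 3 (Study questions) asks for the likely degree of contamination and for the design effects needed to size a definitive trial.

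The section *Protecting against sources of bias and reducing contamination* describes contamination in three ways:

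- As a definition: "people helped to stop smoking with the aid of the LSSS who live in 'clinic only' areas".
- As the purpose of the buffer zones: to "reduce the possibility of people living in control areas crossing into intervention areas and coming across intervention workers".
- As a detection rule: "Contamination would be marked by increases in service use in areas assigned to either the control or special intervention". The rule applies when the rise is absent from the external comparison areas.

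The section adds informal conversations with patients, providers and outreach workers as further evidence.

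Table 2, question 3, takes the design effect from the multilevel analysis. On the other half it says: "Contamination cannot be easily measured; however, we have external controls which will help indicate whether it is occurring".

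The intervention section states the expected effect: "We hypothesise that the 'clinic + outreach' model will attract more patients to the service".

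Table 3 classifies each area's resident users in the baseline year by where they used the service. One column is headed "Number of smokers using LSSS in other areas of randomisation".

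**The concern.** A detection rule for contamination should respond to spill-over and stay silent when there is none. This one also responds to the intervention working as intended, because a rise in the intervention areas that is absent outside satisfies it. The definition does not help. Control-area men helped by the local stop smoking service are receiving the control condition, as the description of the clinic-only arm shows. Only the buffer-zone sentence states the exposure that matters, which is control-area residents meeting intervention workers.

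The article calls contamination the main likely source of bias, and the pilot is meant to inform the sample size of a definitive trial. If the rule is applied literally, the pilot could report contamination where there was none, and the reader could not tell that from real spill-over. The plan also does not name Table 3 as a contamination measure, although it already holds part of the evidence.

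**Working it through.** **Step 1: the rule when there is no contamination.** The article gives no contamination figure to reproduce, so this is a check of logic with assumed values. Let each ratio be service use in the intervention year divided by use in the baseline year. The rule as written signals contamination if the control ratio or the intervention ratio exceeds the outside ratio. The restricted rule signals it only if the control ratio does.

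| Outside | Control | Intervention (assumed) | Rule as written | Control areas only |
|---|---|---|---|---|
| 1.0 | 1.0 | 1.2 | signals | silent |
| 1.0 | 1.0 | 1.5 | signals | silent |
| 1.0 | 1.0 | 2.0 | signals | silent |

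Spill-over is zero by construction in every row. If the control ratio did rise above the outside ratio, both rules would signal. The written rule thus gives the same answer for a pure effect and for real spill-over.

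**Step 2: what Table 3 already holds.** Each of the 16 rows adds up: own area + other randomised areas + outside the study zone + unidentified = total users. The column sums are:

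- own area: 197/563 = 35.0%
- another randomised area: 36/563 = 6.4%
- outside the study zone: 301/563 = 53.5%
- unidentified: 29/563 = 5.2%
- check: 197 + 36 + 301 + 29 = 563

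Among users with a known location, 36/(563 − 29) = 36/534 = 6.7% used another randomised area. If all unidentified users are counted as well, the figure is (36 + 29)/563 = 65/563 = 11.5%.

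The crossing is uneven. Areas 4 to 7 have 79 + 155 + 136 + 98 = 468 users, of whom 4 + 2 + 5 + 0 = 11 crossed. The other 12 areas have 563 − 468 = 95 users, of whom 36 − 11 = 25 crossed (26%).

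**Step 3: what Table 3 cannot give.** Crossing to another randomised area may be within the same arm, and the allocation of each numbered area appears only in figures not available here. The number of control-area residents using an intervention-area service at baseline therefore lies between 0 and 36, or 0 and 65 with the unidentified. As a share of control-area users alone it cannot be computed, because that denominator is unknown, and the pooled 6.4% is not its upper limit.

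**The case against.** **The sentence may mean a rise in both trial arms that is absent outside.** That would be a sensible pattern to look for, but the words are *either* and *or*. Even on this reading, the informative part is the rise in the control areas, which the restricted rule keeps.

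**Question 3 speaks of contamination of both kinds of area.** Intervention-area residents who use control-area clinics would have their exposure diluted. A rise in use in intervention areas does not mark that either.

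**The definition is shorthand that the buffer-zone sentence explains.** This is fair: few readers would take all control care as contamination. It remains a needed wording correction.

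**No effect estimate depends on the rule.** This stands. The effect comes from the group term in the Poisson model and from the comparison of changes.

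Three stronger readings are tempting, and the documents do not support them.

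- *That question 3 cannot be answered.* The design effect comes from the multilevel model. The control-versus-outside contrast contained in the rule still gives an indirect signal, supplemented by the informal conversations.
- *That the trial's data measure contamination directly.* Table 3 measures place of service. Outreach workers also work in non-clinic venues and assist existing providers, and the listed contents of the routine records name no outreach-worker field. Table 2's caution about measurement is therefore fair.
- *That the outside areas are compromised because 53.5% of use was out of zone.* That figure is where trial-area residents attended. The outside comparison is defined by residence, in areas described as mostly distant, and nothing shows that their residents share those clinics.

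**Conclusion.** The contamination rule is wrong as written. It labels the hypothesised rise in intervention areas as contamination, at every assumed effect size tried and with no spill-over present. It also conflicts with the buffer-zone sentence in its own section, and the accompanying definition describes control care. The consequence is limited to the contamination half of primary question 3, which is answered ambiguously.

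The logical conclusion rests on the text alone; the rate ratios only illustrate it. The Table 3 figures are baseline counts of use in any other randomised area and do not estimate cross-arm contamination. The point is worth correcting before the pilot's contamination result is reported, because that result is meant to serve the definitive trial.

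**What to change.** 1. Apply the outside-area comparison of change to the control areas only.
2. Reword the definition so that it refers to control-area residents reached by outreach workers or by outreach-supported services.
3. Repeat Table 3 for the intervention year, split by arm. Report the share of control-area residents' quit dates set at providers in intervention areas, before and during the intervention, as a partial index of contamination, with the unidentified services shown.
4. If the records identify outreach workers, also report the share of control-area residents' quit dates set with one. Do not subtract a baseline from this share. Nor should a baseline location share be subtracted for outreach-supported clinics: control-area men who already attended such a clinic become exposed when support begins, and the subtraction would cancel that exposure.

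The cost is two changes of wording and one further tabulation of routine records. The section on current study status says that analysis is under way, so this is still possible. The intervention year has ended, so step 4 depends on fields already recorded.

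The index misses contact in non-clinic venues and at unidentified services. The outside-area contrast and the informal conversations should therefore stay alongside it.
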